#### Randomization and blinding

After in-person eligibility confirmation and written informed consent at the laboratory visit, participants are randomly allocated to experimental or control groups in a 1:1 ratio. Computer-generated randomization using Python employs permuted block randomization to allocate 46 participants to each group. Randomization occurs after enrollment and before baseline assessment (T0) and first intervention session. Participants remain blinded to group allocation, understanding they are participating in VR-based interview presentation and relaxation training research without knowing whether they belong to experimental or control groups. While researchers are not blinded during experimental procedures, data analysis and report writing are completed with participant group information blinded, with interpretation beginning only thereafter. Future outcome reporting papers will present blinded report versions as reference materials.

#### Confidentiality and data management

Study data will be stored on encrypted, password-protected laboratory computers with restricted access. Personal identifiers and research data will be stored separately using coded study identification numbers. The file linking participant identities to study IDs will be maintained separately and will be accessible only to the designated monitoring investigator. Data quality will be monitored through ongoing review of study records and weekly cross-checks of questionnaire, physiological, and scheduling data. Secure monthly backups will be performed. Access to the final de-identified dataset will be limited to the first author and the monitoring investigator unless additional access is required for approved analyses.

#### Data preparation and planned analyses

Missing participant data are included in analyses for intention-to-treat (ITT) analysis. ITT analysis preserves randomization principles while reflecting actual clinical environments, analyzing all randomly allocated participants according to their original group assignments regardless of dropout or protocol violations [51]. Primary and secondary analyses of self-report questionnaires outcomes will be conducted using linear mixed-effects models, with fixed effects for group, assessment occasion, and their interaction, and participant-specific random effects to account for within-subject correlation across repeated measurements.

PPG data undergo preprocessing using third-order Savitzky-Golay filters, with heart rate variability analyzed in the time domain to capture short-term autonomic responses. Primary analyses compare PPG-derived, time-domain HRV and heart rate measures between groups during key intervention phases (interviewer questioning, presentation, and stabilization) to assess short-term autonomic reactivity. The primary outcome is ΔRMSSD (presentation minus baseline stabilization), representing parasympathetic reactivity. Secondary analyses include comparisons of mean HR, ΔHR, SDNN, and pNN50 to capture overall autonomic activation and variability. Long-term habituation patterns will be examined by modeling within-subject slopes of ΔRMSSD and ΔHR across the three sessions, with an anticipated progressive reduction in reactivity in the experimental group.

GSR signals are decomposed into tonic (SCL) and phasic (SCR) components using Continuous Decomposition Analysis [48, 52]. For between-group comparisons, phasic response magnitude to interviewer questions are analyzed across sessions. Tonic arousal levels are compared between groups throughout the entire intervention period. Within the experimental group, GSR responses across the sequential positive, neutral, and negative interviewer-reaction stages will be explored in relation to concurrent self-report and behavioral anxiety indicators. Because these stages are delivered in a fixed sequence as part of a single graded intervention package, these analyses will be interpreted as exploratory and will not be used to infer the independent causal effect of each reaction valence.

Motion Energy Analysis (MEA) quantifies movement patterns using 10 frames per second video conversion and gray-scale pixel differencing methodology [49]. Motion energy vectors undergo standard smoothing and z-transformation procedures. Given that control group interviewers remain static, synchronization analysis focuses on within-experimental group patterns. Following established MEA protocols, 4-min interaction segments (question → presentation → interviewer reaction) are analyzed using 30-s sliding windows with cross-correlations computed for time-lags up to ±5 s in 0.1-s steps [49].

Voice analysis examines 1-min presentation recordings using automated prosodic feature extraction. Speech samples will be preprocessed with noise filtering but not segmented into fine-grained phonetic units, as analyses focus on suprasegmental prosodic patterns. Primary measures include fundamental frequency (F0) mean, speech rate, and pause ratio, which together reflect expressive and arousal-related vocal behavior. All features will be within-subject standardized relative to baseline readings to control for inter-individual variability. Voice features will be compared between groups and across sessions, with correlation analyses examining relationships between prosodic stress indicators (e.g., elevated F0, reduced speech rate, increased pause ratio) and concurrent anxiety measures. Expected patterns include higher F0 and slower, less fluent prosodic dynamics in early sessions, followed by progressive normalization indicating reduced performance anxiety [53].

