### Sample size

The primary outcome is public speaking anxiety as measured by the PSAS, assessed at six prespecified assessment occasions (baseline; immediately after each of the 3 sessions; 6- and 12-week follow-ups). The study is powered to detect a group-by-assessment-occasion interaction reflecting between-group differences in change from baseline in PSAS across repeated assessments.

Previous meta-analyses demonstrate that VRET produces large effects versus waitlist conditions (*g* = 0.90) and shows comparable efficacy to in vivo exposure therapy [16, 34]. However, since both groups in the present trial receive active PSA training, we anticipated only a small incremental effect. Our intervention extends standard VR exposure by introducing graded interviewer reactions delivered as sequential components of a single exposure package. Research indicates that social-evaluative characteristics of virtual audiences can influence performance confidence and anxiety responses, with some improvements transferring to real-world public speaking performance [25, 34].

Based on these findings, a conservative effect size of *f* = 0.15 was assumed for between-group differences in repeated outcome change. A priori power analysis using G*Power (ANOVA: repeated-measures, within-between interaction; *α* = 0.05, 1 − β = 0.80, two groups, six measurements, correlation among repeated measures = 0.50, nonsphericity correction *ε* = 0.50) indicated a total sample of *N* = 78. Although the primary analysis will use a linear mixed-effects model, the sample size was calculated using a repeated-measures ANOVA framework focusing on the group-by-assessment-occasion interaction. This interaction corresponds to the primary estimand of interest and aligns with the primary analysis model. The ANOVA-based approach was adopted as an approximation because prior data were insufficient to parameterize variance components required for LMM-based simulation. To account for approximately 15% attrition commonly observed in VR exposure studies [35], the recruitment target was set at 92 participants (46 per group). Figure 1 shows the CONSORT flow diagram for the recruitment process.

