#### Participant timeline: schedule of enrollment, interventions, and assessments

### Outcome measurement

#### Primary outcome

Public Speaking Anxiety Scale (PSAS): The primary outcome measure is change from baseline in Korean-version PSAS total scores at each post-baseline assessment occasion (T1–T5), with assessments conducted at baseline (T0), immediately after each intervention session (T1, T2, and T3), and at 6-week (T4) and 12-week (T5) follow-ups. The PSAS is a 17-item self-report questionnaire comprising cognitive, behavioral, and physiological dimensions of public speaking anxiety [39]. The scale demonstrates good psychometric properties and is well-suited for monitoring public speaking anxiety treatment effects [40]. The primary estimand is the between-group difference in mean change from baseline in PSAS total scores across post-baseline assessment occasions, estimated using a linear mixed-effects model with fixed effects for group, assessment occasion, and their interaction.

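### The primary PSAS model has no baseline adjustment, so the treatment contrast is unbiased but less precise than the data allow

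*Protocol article*

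**What the plan says.** The primary outcome section defines the outcome as change from baseline in PSAS at T1 to T5. It defines the estimand as the between-group difference in mean change across those occasions, "estimated using a linear mixed-effects model with fixed effects for group, assessment occasion, and their interaction". The abstract lists the same fixed effects. The section on data preparation and planned analyses repeats them for all self-report outcomes and adds how correlation is handled: "with fixed effects for group, assessment occasion, and their interaction, and participant-specific random effects to account for within-subject correlation across repeated measurements".

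None of the three places lists baseline PSAS as a covariate or sets the arms to a common mean at T0. The article does not say whether T0 is a sixth response or is subtracted first. It also does not say whether the random effects are an intercept only or include a slope.

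The sample size section works from a repeated-measures ANOVA interaction with "correlation among repeated measures = 0.50" and "nonsphericity correction *ε* = 0.50". It describes this interaction as matching the primary analysis model.

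T0 is collected after randomization and before the first session (Screening; Randomization and blinding).

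**The concern.** With only group, occasion and their interaction, any contrast against T0 is a plain change-score difference. Subtracting baseline in full is the most efficient use of it only when the later score moves one for one with baseline. At any lower correlation, regression on baseline gives a smaller variance from the same data.

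This matters here because the sponsor expects only a small added effect over an active VR control. T0 PSAS is already scheduled for every participant, so the lost precision could be recovered without extra visits or participants.

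A second, smaller question concerns the covariance. The sample size allows for marked nonsphericity, which is plausible because the sessions are 48 hours apart while the follow-ups come 6 and 12 weeks after the third session. The stated model names nothing that plays the role of that correction.

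**Working it through.** **Inputs.** From the sample size section: f = 0.15, α = 0.05, power 0.80, two groups, six measurements, ρ = 0.50, ε = 0.50, N = 78 (39 per arm), 15% attrition, target 92. Assumptions of this review: common SD σ = 1 at each occasion, complete data, and the correlation patterns named below.

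**1. The plan's own figure.** λ = f²·N·m·ε/(1 − ρ) = 0.0225 × 78 × 6 × 0.50/0.50 = 10.53, with df1 = 5 × 0.50 = 2.5 and df2 = 76 × 2.5 = 190. Power is 0.801 at N = 78 and 0.796 at N = 77, so 78 reproduces. 78/0.85 = 91.8 gives 92. With ε = 1 the same inputs need only N = 50.

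**2. Precision.** Let v be the variance of the average of the chosen post-baseline occasions and c its covariance with T0. Per participant:
- change score: v + 1 − 2c
- baseline-adjusted: v − c²
- saving: (1 − c)²

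With equal correlations ρ and k occasions averaged, v = (1 + (k − 1)ρ)/k and c = ρ. At ρ = 0.50 the saving is 0.25 each time. The detectable difference is 2.80·√(4 × variance/78).

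| Contrast | Change | Adjusted | Reduction | Detectable difference (SD) |
|---|---|---|---|---|
| One occasion | 1.00 | 0.75 | 25% | 0.63 → 0.55 |
| T4/T5 mean | 0.75 | 0.50 | 33% | 0.55 → 0.45 |
| T1–T5 mean | 0.60 | 0.35 | 42% | 0.49 → 0.375 |

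Where the change-score contrast has 80% power at 39 per arm, the adjusted one has about 96% (T1–T5 mean) or 90% (T5). For ρ from 0.3 to 0.8 the reduction for the T1–T5 mean runs from 58% (0.84 to 0.35) to 17% (0.24 to 0.20).

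The joint 5-df test gains unevenly. Where the unconstrained model has 80% power, a common T0 mean gives 97% for a constant effect, 91% for a linear one and 81% for an effect at T5 only.

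**3. A nonspherical pattern.** Assume correlations of 0.85 within T0–T3, 0.30 between T0–T3 and T4/T5, and 0.50 between T4 and T5. This gives ε of about 0.49.
- T1, T2 or T3: 0.300 to 0.2775, a 7.5% reduction
- T5: 1.40 to 0.91, 35%
- T4/T5 mean: 1.15 to 0.66, 43%
- T1–T5 mean: v = (5 + 2 × 4.85)/25 = 0.588 and c = 0.63, so 0.328 to 0.191, 42%

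**4. Random intercept only, same pattern.** The mean correlation is (6 × 0.85 + 8 × 0.30 + 0.50)/15 = 0.533, so the model takes the residual variance as 0.467.
- T4/T5 mean minus T0: the model uses 0.467 × 1.5 = 0.70 and the truth is 1.15. The effective cut-off is 1.96 × √(0.70/1.15) = 1.53, a two-sided error of about 12–13%. Simulation gave 12.3–12.4%.
- T1–T5 mean minus T0: the model uses 0.467 × 1.2 = 0.56 and the truth is 0.328. The cut-off is 2.56, an error of about 1%. Simulation gave 1.1%.
- T1 or T3 minus T0: under 0.1% in simulation.
- Interaction, 5 df: 8.7–8.9% in simulation. The Box approximation at ε = 0.50 gives 9.7%.

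Under three other assumed patterns (ε 0.50 to 0.62), the uncorrected interaction test had 7.6–9.1%. With a random intercept plus slope it had 5–7%.

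**The case against.** **The analysis is valid as written.** A change-score contrast is unbiased under randomization and matches the declared outcome. N = 78 was computed for the unadjusted interaction and reproduces. All of this stands: the cost is efficiency, and the plan is not underpowered on its own assumptions.

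**The gain is not uniform.** The 25–42% figures assume equal correlations, and for closely spaced session assessments the gain may be small. This stands too. The gains for the follow-up and averaged contrasts remain under the nonspherical pattern.

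**T0 follows randomization, and the researchers are not blinded.** Adjustment therefore assumes that allocation did not affect T0. That should be said, but the change score needs the same assumption, and participants are described as blinded.

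**A reader might infer that the primary test has an inflated type I error.** The article does not support that. It says only that there are participant-specific random effects. An intercept-only structure is one reading, and covariance structure and degrees of freedom are commonly left to an analysis plan. The ε of 0.50 is a planning input, not an estimate, and the article calls its ANOVA calculation an approximation. Even with an intercept alone, the averaged contrast, one natural reading of the estimand, was conservative in the pattern above. What remains is a mismatch between the sample size and the stated model, and a possible miscalibration in either direction.

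**Conclusion.** The point holds as a loss of precision. The primary model is stated three times without baseline adjustment. At ρ = 0.50 with equal correlations, this forgoes a variance reduction of 25% (one occasion), 33% (T4/T5 mean) or 42% (T1–T5 mean). The size depends on correlations that the article does not know, and it falls to about 7.5% for early occasions correlated 0.85 with T0. There is no bias, and no error in the sample size arithmetic.

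The covariance point is secondary and conditional. It applies only if the random effects are an intercept alone and no corrected or robust test is used. Under one assumed pattern, the error would then be about 9% for the interaction, about 12% for the late follow-up contrast and about 1% for the T1–T5 mean.

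**What to change.** State one of two forms for PSAS, and use the same form for LSAS-SR and FNE-B:

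1. T1–T5 as responses, with group, occasion, group × occasion, baseline score and baseline × occasion.
2. All six occasions as responses, with a common T0 mean for both arms.

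Under form 1, take the primary test from the group contrast averaged over T1–T5, or from the joint test of group plus group × occasion. The group × occasion term alone would miss an effect that is constant over T1–T5.

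Add a sentence that T0 is collected after randomization and that adjustment assumes allocation did not influence it.

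Specify an unstructured covariance over the fixed occasions with Kenward–Roger degrees of freedom, and name a fallback for non-convergence, such as heterogeneous Toeplitz. This removes the dependence on sphericity.

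The cost is wording and some extra nuisance parameters: at most 6 × 7/2 = 21 covariance parameters with 92 participants planned. Sample size, visits and outcomes stay as they are. The change should be recorded before any analysis by group.

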#### Pre-session voice recording and stabilization before each session

Participants receive brief study explanations before donning Head-Mounted Displays (HMD) and physiological monitoring equipment (Shimmer3 GSR + unit; Shimmer Sensing, Dublin, Ireland). Following equipment setup, participants produce 1) a 5-s sustained vowel/a/(“ah ~ ”; the central 3 s analyzed) and 2) a continuous reading passage from the standardized Korean paragraph “Fall” (Kim, 1996; see Appendix A for full text, IPA transcription, and English translation), which provides balanced phonemic coverage and is widely used for voice and speech assessments [36]. These recordings will be analyzed for fundamental frequency (F0), intensity, pause duration, and speech rate as baseline prosodic indicators. The sustained vowel duration aligns with CAPE-V recommendations for stable phonation [37]. The passage length was selected to ensure sufficient voiced material for reliable acoustic and temporal analyses, as long-term speaking-rate measures typically stabilize within ~8–16 s [38].

After the voice recording, participants undergo a 3-min stabilization period during which they fixate on a small black dot displayed at the center of a blank VR screen. This stabilization phase allows physiological indicators to reach baseline levels and facilitates adaptation to the VR environment. The interview simulation then proceeds automatically. At Session 1, these measures form part of the study baseline assessment (T0); analogous pre-session recordings in Sessions 2 and 3 are used only for within-session standardization and are not additional baseline assessments.

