#### Secondary outcomes

Liebowitz Social Anxiety Scale-Self Report (LSAS-SR): Used to measure social anxiety which is highly related to public speaking anxiety. LSAS-SR is a 48-item scale assessing anxiety and avoidance levels across 24 social situations, with the Korean version validated for university students [41]. The scale demonstrates excellent internal consistency (*α* = 0.92–0.95) [41]. LSAS-SR total scores will be summarized at the group level and compared across the same six assessment occasions used for the primary outcome (T0–T5). 

Fear of Negative Evaluation-Brief (FNE-B): A 12-item scale measuring fear of negative evaluation. Originally developed by Watson and Friend (1969) and shortened by Leary (1983) [42], the Korean version was validated by Lee and Choi (1997) [43]. Items are rated on a 5-point Likert scale, with higher scores indicating greater fear of negative evaluation [44]. FNE-B total scores will be summarized at the group level and compared across the same six assessment occasions used for the primary outcome (T0–T5). 

Physiological indicators: To objectively compare short-term anxiety induction levels and long-term desensitization patterns between groups during exposure, photoplethysmography (PPG) for heart rate measurement and galvanic skin response (GSR) measurement are implemented [45]. For cardiac autonomic activity, the principal variables will include RMSSD and SDNN (log-transformed if distributional assumptions are violated), and pNN50, derived from PPG signals collected from the earlobe at 256 Hz. For electrodermal activity, the principal variables will include mean tonic skin conductance level (SCL) and phasic SCR peak amplitude and peak count derived from GSR signals collected from the index and middle fingers of the non-dominant hand at 256 Hz. These participant-level physiological variables will be summarized by session and compared between groups across intervention stages. Signals will be processed using third-order Savitzky-Golay filters to preserve signal strength while providing smoothing [46]. Heart rate variability reflects autonomic nervous system responses to stress and anxiety [47], while galvanic skin response serves as an indicator of sympathetic nervous system arousal levels [48].

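### Tonic skin conductance is planned as a mean level with no stated stabilization reference, leaving avoidable person-to-person variance in the group contrast

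*Protocol article*

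**What the plan says.** Three sections of the protocol article bear on this.

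- **Secondary outcomes** defines the variables: "For electrodermal activity, the principal variables will include mean tonic skin conductance level (SCL) and phasic SCR peak amplitude and peak count". It adds: "These participant-level physiological variables will be summarized by session and compared between groups across intervention stages".
- **Data preparation and planned analyses** gives the tonic comparison: "Tonic arousal levels are compared between groups throughout the entire intervention period". The phasic component is handled separately, as response magnitude to the interviewer's questions.
- **Pre-session voice recording and stabilization before each session** describes the resting recording: "participants undergo a 3-min stabilization period during which they fixate on a small black dot". Its purpose is stated: "This stabilization phase allows physiological indicators to reach baseline levels and facilitates adaptation to the VR environment". The same section ends by saying that "analogous pre-session recordings in Sessions 2 and 3 are used only for within-session standardization and are not additional baseline assessments".

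Two other signals have an explicit reference. For heart rate variability: "The primary outcome is ΔRMSSD (presentation minus baseline stabilization), representing parasympathetic reactivity". For voice: "All features will be within-subject standardized relative to baseline readings to control for inter-individual variability".

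**The concern.** The physiological indicators are meant to compare anxiety induction during exposure, and desensitization over the sessions, between the arms. SCL is given as a level, and no text ties it to the person's own resting value. The limitations paragraph of the Discussion itself says that these indicators vary between individuals. The protocol deals with this for RMSSD, heart rate and voice, but does not say that it does so for SCL.

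The stabilization period exists at every session, and the sensor is fitted before it starts, so a resting SCL should be available at no extra cost. An analysis that ignores it carries all resting variation between people into the group contrast. That makes a real difference harder to detect and leaves the estimate more exposed to chance imbalance in resting level.

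The window matters too. Under Third session, only the format of the interviewer reaction is said to differ between arms. Stabilization and the coping exercise are common to both. If SCL is averaged over the full recording, part of that average cannot differ by design, apart from carry-over of arousal.

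**Working it through.** **1. The plan's own figures.** None is given for SCL: no SD, effect size or baseline correlation. The stated sample size concerns PSAS only. It reproduces: with f = 0.15, six measurements, correlation 0.50 and ε = 0.50, power at N = 78 is 0.801, and 78/0.85 = 91.8, so 92. Nothing below alters it. It is used only for 78/2 = 39 evaluable participants per arm.

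**2. Precision.** Let ρ be the correlation between stabilization SCL and interview-phase SCL, with equal variances. Relative to the variance of the raw level:

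- covariate adjustment leaves 1 − ρ²;
- a simple change score leaves 2(1 − ρ).

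The difference detectable with 80% power at two-sided 5%, with one mean per participant, is (1.96 + 0.8416) × √(2/39) = 2.8016 × 0.22646 = 0.634 raw SD without adjustment. With adjustment it is multiplied by √(1 − ρ²).

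| ρ (assumed) | Adjusted, 1 − ρ² | Change score, 2(1 − ρ) | Detectable difference, adjusted (raw SD) |
|---|---|---|---|
| 0.3 | 0.91 | 1.40 | 0.605 |
| 0.5 | 0.75 | 1.00 | 0.549 |
| 0.7 | 0.51 | 0.60 | 0.453 |
| 0.8 | 0.36 | 0.40 | 0.381 |
| 0.9 | 0.19 | 0.20 | 0.277 |

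Covariate adjustment gains at any positive ρ. A change score gains only above 0.5 and loses below it.

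**3. Time in which the arms can differ.** Stated durations are stabilization 180 s, preparation 20 s, answer 60 s and coping exercise 120 s. The question and reaction have no stated length; 10–60 s is assumed. Separately, the motion-energy paragraphs of the analysis section refer to 4-min segments from question to reaction, which is hard to square with 20 s plus 1 min.

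| Reading | Calculation | Share |
|---|---|---|
| Stabilization counted, assumed 10–60 s | 90/390 to 140/440 | 23–32% |
| Stabilization not counted, assumed 10–60 s | 90/210 to 140/260 | 43–54% |
| Stabilization counted, 4-min segment | 240/(180 + 240 + 120) | 44% |
| Stabilization not counted, 4-min segment | 240/(240 + 120) | 67% |

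The share therefore runs from 23% to 67%, depending on the reading.

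**4. Which stabilization can serve as baseline.** Session 1 stabilization comes after randomization but before any content that differs between arms, so it is a proper pre-intervention covariate. Stabilization at Sessions 2 and 3 follows earlier treatment. Adjusting for it, or subtracting it, isolates reactivity within that session and can remove carry-over or habituation, which is part of what the trial wants to see.

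**The case against.** The strongest reply is that much of this is silence rather than error. The article does not call SCL unreferenced, and its sentence on within-session standardization follows directly on the description of stabilization, so it may include GSR. A reader might infer that the stabilization recording is not used for SCL at all. The documents do not establish that: they neither name GSR there nor exclude it.

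A reader might also infer that SCL will be pooled into one average and that a real difference will shrink to a quarter or a third of its size. That is not supported either. Secondary outcomes speaks of summaries by session and comparison across stages, and the entire intervention period may simply mean all three sessions. The section heading places stabilization before each session, which argues against counting it. Arousal may also persist into the coping exercise. The dilution thus holds under one reading only.

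Nor is SCL the trial's main electrodermal endpoint. It is listed with SCR amplitude and count, and question-locked phasic responses are planned. A sustained tonic measure beside an event-locked one is a defensible pairing, particularly as desensitization is also an aim.

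Finally, the article condenses a fuller plan, which may set epochs and covariates. That would excuse silence alone. But the article does state a window and a variable for SCL, and it states a reference for RMSSD in the same section. The missing reference, and the unclear relation between the three sections, therefore remain.

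**Conclusion.** The point holds as a loss of precision on one secondary variable. As written, the SCL comparison names no resting reference although one is recorded at every session. It is not a bias: randomization protects the comparison, and chance resting differences are ordinary sampling variation. PSAS and the sample size are unaffected.

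The size depends on an assumed ρ. Adjustment would remove 25%, 49% and 81% of the variance at 0.5, 0.7 and 0.9, but only 9% at 0.3. For Sessions 2 and 3 the relevant ρ runs across visits and may be lower than within a session. A prediction that the SCL comparison will read as null goes beyond the documents, because no SCL effect or SD is given. The dilution cannot be fixed to one figure.

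**What to change.** State the tonic analysis as follows.

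1. **Main SCL comparison:** mean SCL in the interview/presentation phase, per session, compared between groups with Session 1 stabilization SCL as a covariate.
2. **Within-session reactivity:** interview-phase SCL adjusted for, or minus, that session's stabilization SCL, parallel to ΔRMSSD. Adjustment is the safer form, since a change score gains only if ρ exceeds 0.5.
3. **Stabilization SCL by session and arm,** reported separately, so that carry-over or habituation is not removed unseen.
4. **Whole-period level** kept as a supporting summary, with its window defined.
5. **Reconcile** the stabilization section, Secondary outcomes and the analysis section: say whether within-session standardization covers GSR, and what the entire intervention period includes.

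The cost is wording and slightly more analysis work; no new data are needed. The downside is that session-specific referencing measures reactivity rather than overall level, which is why items 1 and 3 should stand beside item 2.
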